#### Secondary analyses

Random effects analysis of treatment outcomes as a function of time will also be employed to analyze associations with questionnaire data and observer ratings (SPAI, SPK, SPV, BSPS, BDI, EQ-5D, ASQ, HAQ, STEPP, reaction to treatment, CGI). Moreover, analyses to be performed will include the following: cross-sectional analyses as above; analyses of subjects’ and therapists’ conditions regarded as subgroup; SP treatment costs (CSSRI)
[38] will also be considered as ‘process variables’; again, a one-sided level of significance at α = 0.05 will be chosen (see Discussion).

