### Sample size calculation

The only study directly comparing performance of therapy delivered under RCT conditions and routine care refers to group CBT for social phobia
[18] and showed a small but significant advantage for the RCT therapies. The difference between the Clark trials
[17,18] and other controlled trials suggests a much higher difference in the to-be expected between-group effect sizes of our study but only under the improbable assumption that trained private practitioners will be comparably successful as the specialized therapists in the Clark trials. Sholomskas *et al.*[39], in a study directly testing the effects of additional training, but not in the field of SP, reported an average between group effect size of d = 0.69 when comparing therapists who were trained in a seminar plus supervision and therapists who used a manual without further training with regard to their performance in standardized role plays. However, this estimation does not directly refer to the expected effect sizes for the therapeutic benefit, which is the main outcome criterion of this trial. Given this inconsistent information, we choose to expect a more conservative effect size of d = 0.50 between Group 1 (trained therapists) and Group 2 (treatment-as-usual), for pragmatic reasons. We aimed at estimating the sample size needed for a dichotomous approach (remission rates according to the above defined criterion, LSAS <30). In order to assure comparability with the parallel trial for psychodynamic therapy
[37] we introduced the same conservative assumptions: (1) the ICC was set to 15% which is high compared to similar studies
[40]; and (2) for the primary analysis (ITT) drop-outs will be analyzed as patients with no remission. When assuming <50% remitters and an equal drop-out rate in both conditions, the absolute difference between remission rates will remain unchanged, but the relative difference will be much greater and will substantially enlarge the difference between treatments.

In contrast to Wiltink *et al.*’s study protocol
[37], the average number of patients in a cluster was assumed to be five, as we choose to collaborate more continuously with the included therapists. Please note that this is the only assumption differing from those made in
[37] resulting in a higher *a priori* sample size than in
[37].

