In order to detect a difference between Groups 1 and 2 at α = 0.05 (one-tailed; see Discussion) with a power of 0.80, *n* = 58 patients per group are required according to the formula of Campbell *et al.*[40,41] for cluster-randomization, given that five patients per therapist will be treated (for a more comprehensive account, see
[42]):

$$N=2*{\left[\frac{\sigma (z_{\alpha }+z_{\beta })}{E}\right]}^{2}*\left[1+(m-1)\rho \right]=2*{\left[\frac{\left(z_{\alpha }+z_{\beta }\right)}{ES}\right]}^{2}*\left[1+(m-1)\rho \right]$$

(z_α_, z-value for probability of error type I alpha; z_β_, z-value for probability of error type II beta; σ, standard deviation of outcome; E, expected ES of outcome; m, mean observations for each cluster; ρ, Intracluster correlation coefficient (ICC); ES = E/σ, standardized effect size)

Given a conservative drop-out rate estimate of 25% (taking into account slightly elevated drop-outs in a practice study), a total of *n* = 162 patients are required to be allocated to the trial. Thus, *n* = 54 patients will have to be included in each center. According to data of the [name] *et al.*[43] study on social phobia, in which patients were recruited in a comparable setting of German psychotherapeutic care, 61% of 250 patients meeting the inclusion criteria can expected to be finally included. We estimate that not more than about 250 patients will have to be assessed for eligibility.

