The present study will also be the first to include systematic CBT training of private practitioners in the field of psychotherapy in the German healthcare system. It will help clarify whether clinical practitioners will generally regard the new CBT approaches as helpful for their work, and ascertain to what degree they will integrate the new methods into their clinical routine. As we specifically expected the new methods to be superior, it needs to be mentioned that we choose one-sided testing and an alpha of 0.05 as appropriate for a superiority trial
[54]. There are two reasons for this decision. Firstly, in the field under investigation there is clear and robust evidence (not just expectation) that the manualized approach of CBT for social phobia according to Clark and Wells is the most efficacious among other CBT treatments (see
[15]). It follows that the scientific hypothesis to be tested is one-sided. Secondly, as our study approach is that of a transfer or dissemination trial of an already established manualized procedure, only a clear advantage of this procedure over the reference intervention (non-manualized treatment) would have consequences for practice. Given these two conditions (that is, one-sidedness of scientific hypothesis and practice relevancy for superiority of the to-be implemented treatment only), we followed the recommendation of authors, such as Bland and Altmann
[55] or Knottnerus and Bouter
[56], and calculated the *a priori* sample size estimation based on one-sided testing. This approach warrants that the sample size is not larger than needed and the study is economic.

However, the clear methodological disadvantage of this decision has to be emphasized: Although it is not our scientific hypothesis, we can certainly not rule out ‘harm’, which in our case would mean superiority of the (non-manualized) reference treatment over the to-be implemented manualized one. Given the logic of the one-sided analysis, no statistical testing whether the standard procedure is superior to the manualized one can be made. Accordingly, a negative result in a superiority trial (like ours) would not prove that the investigated therapies are equivalent
[54].

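### One-sided 0.05 is applied to every secondary analysis, but the reason given covers only superiority of manualized CBT, not associations, process measures, subgroups or centre comparisons

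*Protocol article*

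**What the plan says.** The primary comparison is one-sided. The Sample size calculation section uses "α = 0.05 (one-tailed; see Discussion) with a power of 0.80", and the Primary analyses section sets the alternative as a higher remission probability with manualized treatment.

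The Secondary analyses section then lists:

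- random effects models "to analyze associations with questionnaire data and observer ratings", with eleven instruments named: SPAI, SPK, SPV, BSPS, BDI, EQ-5D, ASQ, HAQ, STEPP, reaction to treatment and CGI;
- cross-sectional analyses of the kind described under Primary analyses, which compare patients and therapists across the three centres;
- subgroup analyses by patient and therapist characteristics;
- treatment costs, handled as process variables.

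The list closes with "again, a one-sided level of significance at α = 0.05 will be chosen" and a reference to the Discussion. The rule exempts nothing on the list.

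The Discussion gives two reasons for one-sided testing. The first begins "in the field under investigation there is clear and robust evidence (not just expectation) that the manualized approach of CBT for social phobia" and goes on to call the Clark-Wells form the most efficacious kind of CBT. The second is that only an advantage of the manualized procedure would change practice. It then concedes that a one-sided analysis cannot test whether standard treatment is better.

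**The concern.** By the article's own argument, a one-sided test needs a one-sided scientific hypothesis. Both reasons in the Discussion concern one contrast, manualized against non-manualized treatment. They do not say whether affective style, alliance, session evaluation or reaction to treatment should relate positively or negatively to outcome. Nor do they say which patient or therapist subgroup should do better, or how three centres should rank.

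Without a stated direction, a one-sided test can be run in two ways, and each has a defect. If the tail is chosen after the data are seen, the per-test error is twice the nominal level. If a direction is assumed but not written down, a result of the opposite sign cannot be tested, although in an exploratory association it would be just as informative. The Discussion accepts that loss for the treatment comparison and says why. It gives no reason to accept it for the other analyses.

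**Working it through.** **Step 1. Which secondary analyses have a direction?** Each item is set against the Objectives and hypotheses, Outcomes and Discussion sections.

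| Secondary analysis | Direction in the article? |
|---|---|
| Between-group contrasts on SPAI, SPK, SPV, BSPS, BDI, EQ-5D, CGI (7 instruments) | Yes: hypothesis 1 expects better treatment effects with trained therapists |
| Treatment costs | Expected: the Discussion anticipates a reduction, but it is not a formal hypothesis |
| ASQ, HAQ, STEPP, reaction to treatment (11 − 7 = 4 instruments) | None stated |
| Patient and therapist subgroups | None stated |
| Comparison of three centres | None stated; three groups have no single direction |

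**Step 2. Thresholds.** The one-sided 0.05 critical value is z(0.95) = 1.645. The two-sided 0.10 value is z(1 − 0.10/2) = z(0.95) = 1.645, which is identical. The two-sided 0.05 value is z(0.975) = 1.960.

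**Step 3. Error per test under the null.**

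- Direction left open: 2 × [1 − Φ(1.645)] = 2 × 0.05 = 0.10.
- Direction fixed in advance: 1 − Φ(1.645) = 0.05, with no test of the opposite sign.

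**Step 4. The four instruments without a direction.** The article gives no correlation between them, so equal pairwise correlation ρ is an assumption, shown over a range. For k null tests and critical value c, with U standard normal,

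P(at least one) = 1 − E[{Φ((c − √ρ·U)/√(1−ρ)) − Φ((−c − √ρ·U)/√(1−ρ))}^k].

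With k = 4:

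| ρ | c = 1.645, direction open | c = 1.960, two-sided 0.05 |
|---|---|---|
| 0.3 | 32% | 17% |
| 0.5 | 29% | 16% |
| 0.7 | 24% | 13% |

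As a check at ρ = 0: 1 − 0.90^4 = 34% and 1 − 0.95^4 = 19%.

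**Step 5. All eleven instruments, as a bound.** With k = 11 and ρ = 0.5 the same formula gives 51% with the direction open and 30% at two-sided 0.05. If every direction were fixed in advance, one-sided 0.05 would give 26%.

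**Step 6. What two-sided testing costs in power.** This illustration borrows the article's planning values: d = 0.50, 58 per group, five patients per therapist and an ICC of 0.15. The design effect is DE = 1 + (5 − 1) × 0.15 = 1.6, and power = Φ(0.50 × √(58/(2·DE)) − c).

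- DE = 1.6: Φ(2.129 − 1.645) = 68.6% one-sided; Φ(2.129 − 1.960) = 56.7% two-sided.
- DE = 1: Φ(2.693 − 1.645) = 85.3% one-sided; Φ(2.693 − 1.960) = 76.8% two-sided.

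The 58 per group is taken as given here. The article's own formula with these inputs gives 2 × [(1.645 + 0.842)/0.50]² × 1.6 = 79.1 per group. That is a separate matter and does not bear on this point.

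**The case against.** The strongest reply is that most of the list does have a direction. Hypothesis 1 predicts superiority, and seven of the eleven instruments measure symptoms, severity, depression or quality of life, where superiority has an obvious sign. The Discussion also expects lower costs. This stands. A reader might infer that the whole secondary block is tested at an effective 0.10, or quote the 51% against 30% for eleven instruments as the size of the problem. The documents do not support either reading. The eleven-instrument figure is an upper bound that ignores stated directions, and with directions fixed one-sided 0.05 gives a lower family-wise rate (26%) than two-sided 0.05 (30%).

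A second reply is that the two harms exclude each other for any single test. This also stands: either the sign follows the data and the error is 0.10, or the sign was fixed and the opposite effect is untestable. The article does not say which would happen. A reader might also infer that unfavourable effects could not be reported at all. The Discussion rules out a test, not an estimate.

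A third reply is that these analyses carry no confirmatory claim, that multiplicity would remain after the change, and that an article leaves per-endpoint detail to the analysis plan. The first two parts are fair and limit the weight of the point. The third does not dispose of it, because the article does not leave sidedness open. It sets a rule for the whole block and cites a reason that fits only part of it.

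**Conclusion.** The point holds for secondary analyses with no stated direction: associations with ASQ, HAQ, STEPP and reaction to treatment, subgroup analyses by patient or therapist characteristics, and comparisons of the three centres. For these the rule is either a two-sided 0.10 test or a test that cannot see one sign. For the four process-type instruments, the excess over two-sided 0.05 in the chance of at least one false positive is about 15 percentage points at ρ = 0.3 and 11 at ρ = 0.7. Those sizes assume all nulls true, equal correlation, one test per instrument and the sign taken from the data.

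The point does not extend to between-group contrasts on the symptom scales, CGI, BDI and EQ-5D, nor, in the 0.10 form, to costs. It does not question the one-sided primary test, which the article argues for and whose drawback it discloses.

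**What to change.** In Secondary analyses, replace the blanket rule with one sentence: one-sided 0.05 applies only to secondary between-group comparisons whose direction is stated in advance; all other secondary analyses (associations, process measures, subgroups, centre and therapist comparisons) use two-sided 0.05 with two-sided 95% confidence intervals. If costs are to be tested one-sided, write the expected reduction down as a directional hypothesis.

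The price is some power in the exploratory analyses that move to two-sided testing, in the illustration above about 9 to 12 percentage points for a contrast of d = 0.50. No new data are needed, and the primary test and sample size stay as they are. The Trial status section describes recruitment as ongoing, so the change can be made before analysis.

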### Safety aspects

Trial progress, monitor data management, and patient safety will be reviewed by the control center for clinical studies (KKS), the Ethics Committee (EC) of the Technische Universitaet Dresden (Germany), and the Data Monitoring and Safety Committee (DMSC).

### Medical complications

Only psychological conditions according to the International Classification of Diseases F00-F99 (‘Mental and Behavioral Disorders’) will be recorded and classified as adverse events. Any deterioration that results in discontinuation of therapy (including suicidal risk and hospitalization) will be notified immediately by the private practitioner. Changes in psychological disorders will also be notified by the therapist and assessed by the diagnostician after session 25 of treatment, as well as 6 and 12 months post-treatment.

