### Participants

Patient inclusion and exclusion criteria are listed in Table
1. The sample fulfilling these criteria are considered representative for social phobia patients qualifying for treatment in an outpatient setting. Assuming a drop-out rate of 25% over a period of 2 years, a total of 162 patients are planned to be enrolled in the study (that is 54 patients in each center; see sample size calculation). Patients will only be able to enrol once in the present trial. Participants will be able to directly contact the trial centre in response to advertisements via the internet, flyers, or newspaper articles. Alternatively, they will be referred to by healthcare practitioners (that is, medical doctors or private practitioners in psychotherapy). Once the diagnostician confirms the patient’s eligibility for the study, the patient will select and contact a therapist from a list of candidates for treatment. Only private practitioners officially listed in the German chambers of psychotherapists will be recruited. Informed consent from both the therapist and the patient will be collected. All therapists will have to be certified in CBT. Inclusion criteria for therapists are broad (that is, any age and gender, living in the area of the trial center) as a function of the naturalistic aspects of the present trial. However, practitioners having recent training (within the last 5 years) in the Clark and Wells treatment of SP
[17] will be excluded from the study. Measures of allegiance to the treatment condition and professional experience will be collected via self-report of the therapists as well as via expert ratings of video-documented sessions.

**Table 1 T1:** Inclusion and exclusion criteria

**Inclusion criteria**	Diagnosis of SP (SCID-I)
	Liebowitz Social Anxiety Scale >30 (>60 for generalized subtype)
	Age 18 to 70 years
	SP must be primary diagnosis (most severe disorder according to ADIS-IV)
	SP patients with co-morbid disorders will be included, provided that SP is the primary diagnosis, thus ensuring a clinically representative sample as well as analyses of subgroups (for example, type of SP, patients with co-morbid depressive disorder)
**Exclusion criteria**	Psychotic disorder
	Prominent risk of self-harm
	Acute substance-related disorders
	Personality disorders except for avoidant
	Obsessive-compulsive or dependent personality disorder (SCID-II) organic mental disorder
	Severe medical conditions

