	Concurrent psychotherapeutic or psychopharmacological treatment, with the following exception: specific psychopharmacological treatments (that is, tranquilizer, hypnotics, neuroleptics, phytopharmaceuticals, and beta-blockers prescribed as anxiolytics) should be terminated prior to therapy onset
	Anti-depressive medication represents no exclusion criterion as long it is reliably and stably consumed

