### Ethical issues

The trial has been approved by the responsible Ethics Committee of the Technische Universitaet Dresden (EK: 183062010) and the Data Safety Monitoring Committee (DSMC). Prior to assessment, patients will be informed about design and procedures, and will be required to give informed consent and may withdraw at any point without any disadvantage. Participating patients will be provided with a treatment consistent with good clinical practice according to the EMEA guidelines (
http://www.emea.eu.int/pdfs/human/ewp/363503en.pdf) for the diagnosis and treatment of SP. Suicidal tendencies will be examined regularly by the private practitioner. Should the need arise, outpatient services will be available and admission to cooperating clinics will also be possible. For further care, patients that cannot be included in the study will either be added to the practitioner’s general waitlist for further diagnosis and treatment or receive information on alternative potential healthcare practitioners upon request.

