## Abbreviations

ANOVA: Analysis of variance; ASQ: Affective Style Questionnaire; ADIS-IV: Diagnostic interview; AE: Adverse event; BDI: Beck Depression Inventory; BMBF: Federal Ministry of Education and Research; BSPS: Brief Social Phobia Scale; CBT: Cognitive behavioral therapy; CRF: Case report form; CGI: Clinical Global Impression scale; CSSRI: Client Sociodemographic and Service Receipt Inventory; DMSC: Data Monitoring and Safety Committee; DSM-IV-TR: Diagnostic and Statistical Manual of Mental Disorders 4th edition, text revision; EC: Ethics Committee; EQ-5D: Quality of life questionnaire; ES: Effect size; HAQ: Helping Alliance Questionnaire; ICC: Intracluster correlation coefficient; ICD-10: International Classification of Diseases; ITT: Intention to treat; KKS : Control center for clinical studies; LOCF: Last observation carried forward; LSAS: Liebowitz Social Anxiety Scale; RCT: Randomized clinical trial; SAD: Social Anxiety Disorder; RTQ: Reaction to treatment questionnaire; SAD: Social anxiety disorder; SAE: Serious Adverse Event; SCID: Structured Clinical Interview for DSM Disorders; SOPHO-NET: Social Phobia Psychotherapy Research Network; SOPHO-PRAX: Study on the transfer of manualized CBT for social phobia into clinical practice; SP: Social Phobia; SPAI: Social Phobia and Anxiety Inventory; SPK: Social Cognitions Questionnaire; STPP: Short-Term Psychodynamic Psychotherapy; SPV: Social Behavior Questionnaire; STEPP: Session evaluation sheet; T1-T7: Time points of assessment.

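### The adverse-event rule admits only F00-F99 conditions, and the notification rule beside it does not bring suicide attempts, self-harm, admissions or deaths into the adverse-event record

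*Protocol article*

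**What the plan says.** Three consecutive sentences in the Protocol article, Medical complications, set out what is captured on safety.

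- The scope of adverse events: "Only psychological conditions according to the International Classification of Diseases F00-F99" "will be recorded and classified as adverse events".
- A notification duty: "Any deterioration that results in discontinuation of therapy (including suicidal risk and hospitalization) will be notified immediately by the private practitioner".
- A diagnostic check: "Changes in psychological disorders will also be notified by the therapist and assessed by the diagnostician after session 25 of treatment", and again 6 and 12 months post-treatment.

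Other sections show that self-harm and suicidality were foreseen. Table 1 (Participants) lists "Prominent risk of self-harm" as an exclusion criterion. Ethical issues states: "Suicidal tendencies will be examined regularly by the private practitioner"; it also provides for admission to cooperating clinics if needed. Safety aspects gives the review of patient safety to the KKS, the Ethics Committee and the Data Monitoring and Safety Committee (DMSC). The term "SAE: Serious Adverse Event" stands in the abbreviation list but is neither defined nor used in the text shown.

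**The concern.** The first sentence is an exclusion, not a gap left for a fuller document to fill: its opening word restricts both recording and classification. A suicide attempt, an act of self-harm, an admission or a death is an event or outcome, whereas the rule admits conditions. The protocol thus watches for suicidality and self-harm, yet its adverse-event definition does not take in the events themselves.

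The second sentence adds a route for some of them, but a conditional one, and it does not say whether a notified case becomes an adverse event. The two sentences leave open whether suicidal risk and hospitalization are inside or outside the record.

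At stake is the completeness of the record from which three bodies are to judge patient safety and from which harms would later be described. Notification also rests on the treating practitioner, who knows whether he or she was trained. A rule based on plainly observable events, identical in both arms, leaves less room for unequal reporting than one based on a judgement of deterioration.

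**Working it through.** No arithmetic applies: the point depends on no rate, error level or sample size. The check sets each kind of event against the three sentences of Medical complications. One assumption is needed, namely that self-harm and death have no code of their own within F00-F99; the article gives only the chapter label.

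| Event | Adverse event under the first sentence? | Notified under the second? | Caught by the third? |
|---|---|---|---|
| New or worsened F00-F99 condition | Yes | If it ends therapy | Yes |
| Suicide attempt, self-harm or psychiatric admission that ends therapy | Only through an accompanying F-condition | Yes | Only as a change in disorder |
| The same, therapy continues | Only through an accompanying F-condition | No | Only as a change in disorder |
| The same, during the 6- and 12-month follow-up | Only through an accompanying F-condition | No: no therapy is left to discontinue | Only as a change in disorder |
| Somatic admission | No | Not clearly; at most if it counts as a deterioration that ends therapy | No |
| Death | Only through an F-condition recorded as well | Not clearly | No |

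The steps behind the table:

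1. **First sentence.** The restriction covers what is recorded as well as how it is classified. An event without a recorded F-condition is therefore outside the adverse-event record. Where an F-condition is recorded, the condition enters the record; nothing requires that the attempt or admission be recorded with it.
2. **Second sentence.** The duty to notify depends on therapy being discontinued. The words in brackets illustrate such deteriorations and do not remove the condition. Nothing says that a notified case is then recorded as an adverse event, and the sentence before it excludes cases without an F-condition.
3. **Third sentence.** This is the only capture that the section names for follow-up, and it is again based on disorders. A patient who harmed himself or herself in follow-up and whose diagnoses did not change would not appear through it.
4. **Other sections.** The regular examination of suicidal tendencies (Ethical issues) is not linked to recording. Safety aspects names the reviewing bodies but not the data they receive.

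Row 2 is partly mitigated by notification. Rows 3 and 4 have no route except through an F-condition or a change in disorder. Somatic admissions and deaths are clearly covered by none of the three sentences.

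**The case against.** The best defence reads the paragraph as a unit: the first sentence sets the diagnostic scope and the second provides expedited reporting of serious deterioration. Suicidality is examined regularly, three bodies review safety, and the listed abbreviation for serious adverse events hints at a procedure in the full protocol. In a trial that compares trained with untrained CBT practitioners, a scope confined to psychological conditions is arguably reasonable, and a journal article need not set out how serious events are classified.

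Part of this stands. The notification route is real, so a reader who infers that suicidal crises and admissions go unreported altogether goes too far: those that end therapy are notified at once. A serious-event procedure may also exist elsewhere. But an entry in an abbreviation list defines nothing, and a fuller document that recorded more would contradict a sentence that says what alone is recorded. The route's dependence on discontinuation is likewise stated text.

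Other inferences should be resisted:

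- **That suicidality is the trial's main risk.** No section ranks risks. Self-harm risk is an exclusion criterion, suicidal tendencies are monitored, and suicidal risk is an example of notifiable deterioration.
- **That effects of stopping medication belong in this point.** Table 1 says that certain drugs "should be terminated prior to therapy onset". That step precedes therapy and is unrelated to the randomized training.
- **That a planned comparison of harms would be biased.** Statistical analysis plans no such comparison between arms.
- **That a number of missed events can be given.** The article states no rate for these events, and some would be caught by notification or by a recorded F-condition.

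**Conclusion.** The point holds as an inconsistency in the stated safety-recording rule. Followed literally, the rule keeps the following out of the adverse-event record unless an F00-F99 condition is recorded too: suicide attempts, self-harm and admissions that do not end therapy, the same events in the 6- and 12-month follow-up, and deaths and somatic admissions. Events that do end therapy are notified, but their status as adverse events is left unstated.

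The size can be given only as scope: all 162 planned patients, both arms, treatment and follow-up. The primary remission comparison is unaffected; the loss is in the completeness of harms data. It should be corrected, because the rule is explicit and the correction is cheap. The conclusion rests on the literal reading of the restriction, on the assumption about ICD coding stated above, and on the absence from the text shown of any serious-event rule that overrides it.

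**What to change.** Reconcile the sentences of Medical complications. Besides new or worsened F00-F99 conditions, state that death, suicide attempt or self-harm, and hospital admission are recorded as adverse events in both arms, from the start of treatment through the 12-month follow-up, regardless of ICD chapter and of whether therapy is discontinued. Say explicitly that cases notified under the existing duty enter the same record. If the full protocol already has a serious-event procedure, refer to it and bring the restriction into line with it. Report these events descriptively by arm.

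This changes recording only, not patient management. It costs one revised paragraph, one line on the case report form, and a small number of additional event reports from the practices.
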